# Community-Based Hypertension Screening to Prevent Stroke in Underserved Urban Neighborhoods in French Guiana: Protocol for a Quasi-Experimental Study

**DOI:** 10.2196/89318

**Published:** 2026-08-27

**Keywords:** hypertension, stroke, community health workers, early detection of disease, medically underserved area

## Abstract

**Background:**

Hypertension is a leading contributor to stroke and cardiovascular disease in underserved populations.

**Objective:**

This study aims to evaluate a community-based hypertension screening intervention in French Guiana’s precarious urban neighborhoods. This trial will assess whether a structured, community health mediator–led intervention reduces stroke incidence among adults residing in socioeconomically precarious areas of the Communauté d’Agglomération du Centre Littoral (CACL).

**Methods:**

This is a 27-month, monocentric, quasi-experimental study conducted in the CACL, targeting neighborhoods classified as precarious. Adults aged ≥18 years will be included unless they are legally protected or decline participation. Trained mediators will deliver blood pressure screening and health education through mobile units and home visits over a 24-month period. Participants with elevated readings will receive referrals and structured follow-up. The primary outcome is the change in stroke incidence before and after the intervention, using Programme de Médicalisation des Systèmes d’Information (PMSI) hospitalization data. Secondary outcomes include changes in the rates of other cardiovascular and renal events and antihypertensive treatment adherence. Comparisons will use interrupted time series analysis, chi-square tests, and regression models. Missing data will be evaluated, and multiple imputation will be applied as needed.

**Results:**

This study was funded in 2022. Patient enrollment began in September 2023. As of September 4, 2025 (the end of field interventions), 23,289 participants had benefited from the intervention, including 10,901 (46.8%) who were formally enrolled and had completed questionnaires. Follow-up telephone calls were completed until December 2025. Data analysis is expected to be completed in the first quarter of 2026, with primary results anticipated to be published in 2026.

**Conclusions:**

This study will determine whether a scalable, community-mediated hypertension screening intervention reduces stroke incidence in underserved populations.

**Trial Registration:**

ClinicalTrials.gov NCT05814068; https://clinicaltrials.gov/study/NCT05814068

**International Registered Report Identifier (IRRID):**

DERR1-10.2196/89318

Despite promising results, several limitations persist in the evaluation of the impact of community-based hypertension screening on stroke incidence [16,17]. Many studies lack robust control groups or use cross-sectional designs, limiting causal inference [18-20]. Self-reported data and office-based BP measurements introduce recall and diagnostic bias, respectively [17,21,22]. Additionally, in socially vulnerable populations, low follow-up rates and limited integration with existing health infrastructure restrict program sustainability [23,24]. Few large-scale studies in low-resource settings, particularly in South America, have analyzed long-term cardiovascular outcomes such as stroke or end-stage renal disease (ESRD), using validated hospitalization data [25,26]. Moreover, evidence is sparse on adherence to referrals and longitudinal prescription patterns following screening, indicating an underexplored area for assessing the intervention’s impact [27].

To address the critical gap in longitudinal data on stroke prevention in low-resource settings, this prospective, community-based, quasi-experimental study was designed to evaluate the impact of decentralized hypertension screening on stroke incidence among adults aged ≥18 years residing in socioeconomically precarious neighborhoods within the Communauté d’Agglomération du Centre Littoral (CACL) region of French Guiana. Using mobile health stations and home visits, trained health mediators will conduct standardized BP assessments and educational interventions, linking individuals with elevated readings to appropriate health care services. The main outcome—hospital-based stroke incidence—will be measured using national administrative datasets, offering novel insights into population-level vascular risk mitigation in underserved communities.

### Objectives

#### Primary Objective

The primary objective is to determine whether a community-based hypertension screening and referral intervention delivered by trained health mediators is superior to standard health service delivery in reducing the incidence of stroke (*accidents vasculaires cérébraux* [AVC]) over a 2-year period, compared to the 5-year preintervention period, among adults residing in the CACL region of French Guiana.

#### Secondary Objectives

The secondary objectives are to evaluate the effectiveness of the intervention in reducing the incidence and mortality of other major cardiovascular and renal outcomes, including acute coronary syndrome (ACS), transient ischemic attack (TIA), peripheral artery disease (PAD), aneurysm, and ESRD; to assess participants’ adherence to referrals and satisfaction with the program; and to evaluate changes in screening coverage and antihypertensive treatment patterns. Comparisons will also be conducted between residents of targeted precarious neighborhoods and those living in nonintervention zones within and outside the intervention area.

## Methods

### Study Design and Setting

This study is a monocentric, prospective, quasi-experimental intervention conducted within the CACL of French Guiana, comprising the communes of Cayenne, Matoury, Rémire-Montjoly, Roura, Montsinéry-Tonnegrande, and Macouria. The intervention targets socioeconomically precarious neighborhoods and aims to evaluate the effectiveness of a community-based hypertension screening initiative delivered through trained health mediators. The study spans a total of 27 months, comprising a 24-month intervention period followed by a 3-month monitoring and follow-up phase (Figures 1 and 2). The intervention is designed to be inclusive and is accessible to all residents within the targeted neighborhoods, regardless of their eligibility for the study or their decision to participate in the research.

**Figure 1 figure1:**
[figure not shown]
Participant workflow during the study.

All interested participants receive a brief health education session covering hypertension awareness, associated dietary and lifestyle recommendations, and guidance on accessing health care entitlements. Participants may also be referred to other health care facilities or professionals in the event of health concerns other than hypertension. Subsequently, each participant undergoes standardized BP measurement using 3 readings spaced 1 to 2 minutes apart, including at least 1 reading from each arm, in accordance with European guidelines. If BP values suggest possible hypertension, participants are referred for medical evaluation either to a local physician or to the Permanence d’Accès aux Soins de Santé (PASS) based on their insurance status.

Suspected cases are provided with a formal referral document detailing the observed metrics to facilitate continuity of care within the health care system.

Participants identified with elevated BP are contacted by telephone at 3 months after inclusion (with an allowable variation of ±1 week) to assess diagnostic follow-through, treatment initiation, and compliance with medical recommendations. During this follow-up, mediators reinforce the importance of ongoing care if lapses are identified.

In parallel, after the mediators have provided oral information about the study, they verify the inclusion (age ≥18 years, residence in the CACL, and absence of legal protection) and exclusion criteria and obtain the participant’s nonopposition to participation. For these participants, an additional structured questionnaire is administered to collect sociodemographic and anthropometric data, cardiovascular history, prior diagnoses, medication adherence, barriers to health care access, and a satisfaction survey.

Withdrawal from the study is permitted at any time without justification and does not affect access to usual medical care. Investigators may also discontinue participation if continued participation is deemed not to be in the participant’s best interest. Reasons for withdrawal or loss to follow-up will be recorded when available.

Figure 2 outlines the stepwise procedure for participant inclusion, assessment, and subsequent actions based on BP results and health insurance status, including interventions, referrals, and follow-up steps.

**Figure 2 figure2:**
[figure not shown]
Study flow diagram. PASS: Permanence d’Accès aux Soins de Santé.

### Participants

Eligible participants will be adults aged ≥18 years residing within the CACL territory, particularly in neighborhoods identified as precarious based on urban, social, or environmental exclusion. There are no restrictions regarding sex or nationality. Inclusion will be based on residency and age only (Textbox 1). Individuals who explicitly express opposition to participation or who are under legal protection (eg, guardianship or curatorship) will be excluded from data collection. Recruitment will occur within ambulatory settings across targeted neighborhoods, where health mediators will actively engage the population through fixed locations, door-to-door outreach, and dedicated information campaigns involving flyers, posters, and local radio messages. Translation support and multilingual team members will ensure accessibility for participants regardless of their native language.

Inclusion and exclusion criteria.
**Inclusion criteria**
Adults aged ≥18 yearsIndividuals residing in the Communauté d’Agglomération du Centre Littoral
**Exclusion criteria**
Individuals who explicitly refuse to participate in the studyIndividuals under legal protection such as guardianship or conservatorship

### Randomization and Blinding

Because this study is nonrandomized and uses a quasi-experimental design, no randomization procedures will be used. Participants will be naturally exposed to the intervention as a function of their geographic residence. To limit assessment bias, the primary outcomes will be based on objective administrative data from hospital discharge records and national health insurance datasets. These datasets are not influenced by participants’ awareness of their inclusion in the study.

### Intervention or Treatment

The intervention will consist of a comprehensive, community-delivered hypertension screening and education program. It will be implemented by 12 trained health mediators organized into 3 teams of 3 to 4 mediators each. The protocol stipulates that each mediator can screen approximately 10 people per day, representing a target of 2000 adults per month. These mediators, certified through a university-level diploma in health mediation or with equivalent field experience, will engage directly with residents in all precarious neighborhoods within the CACL. Each neighborhood will receive at least 1 intervention visit during the 24-month intervention period. The number of visits per neighborhood will be determined based on population size and accessibility. The goal is comprehensive coverage of an estimated population of 50,000 adults in the target neighborhoods.

To maximize reach, each visit will last 1 to 2 days, with mediators establishing fixed screening posts and conducting door-to-door outreach. The quantification of coverage will not be based solely on the number of individuals screened but on the number of neighborhoods fully investigated by the mediators. The intervention will be considered complete for a neighborhood when the minimum number of planned visits has been conducted, when mediators have systematically covered all streets or sectors through door-to-door approaches, or when repeated visits yield diminishing returns.

Given population mobility and the informal nature of precarious settlements, we acknowledge that precise denominator estimation is challenging. Mediators will set up mobile stations or conduct home visits to measure BP triadically according to European guidelines, provide personalized health education focused on hypertension and lifestyle modification, assess health insurance coverage, and guide participants with elevated BP to appropriate health care professionals or social services (eg, general practitioners or the PASS unit). Follow-up will include a structured telephone call 3 months later to assess completion of the medical referral process.

### Mediator Training and Certification

All 12 health mediators completed either a university diploma in health mediation (*diplôme universitaire de médiation en santé*, University of French Guiana) or possess equivalent certified field experience. Prior to intervention deployment, mediators received specific training consisting of clinical training on BP measurement techniques and device use; training on hypertension pathophysiology, complications, and dietary and lifestyle recommendations adapted to local cultural contexts; training on prevention posture, mediation, and individual counseling techniques; and supervised practice sessions with feedback. Mediators work in teams of 3 to ensure multilingual coverage (French, Creole, Portuguese, Spanish, Arabic, English, and indigenous languages as needed). Each team is equipped with validated BP monitors, educational materials, referral forms, and mobile phones for coordination and follow-up.

### Outcome Measures

The primary outcome will be the change in the incidence of stroke comparing the 5-year preintervention period with the 2-year period following the start of the intervention, as recorded in the Programme de Médicalisation des Systèmes d’Information (PMSI) database. Secondary outcomes will include changes in incidence of ACS [28], TIA [29], PAD [30], aneurysm, and ESRD [31] (*insuffisance rénale terminale* [IRT]), as well as all-cause cardiovascular mortality within 1, 2, and 3 years after the intervention. ACS refers to a spectrum of urgent cardiac conditions caused by a sudden reduction in blood flow to the heart muscle due to a partial or complete blockage of the coronary arteries. This group of conditions includes unstable angina and non–ST-elevation myocardial infarction (NSTEMI), both of which require prompt diagnosis and individualized treatment strategies to prevent further cardiac damage and improve patient outcomes.

ESRD represents the final and most advanced stage of chronic kidney disease, defined by a severely reduced GFR of less than 15 mL/min/1.73 m^2^. At this stage, patients require kidney replacement therapy, which includes either long-term dialysis or kidney transplantation. ESRD is a chronic condition that typically arises in the context of long-standing comorbidities, notably hypertension.

PAD is a circulatory condition characterized by the narrowing or blockage of peripheral arteries, most commonly in the lower limbs, due to the buildup of atherosclerotic plaques. This reduced blood flow can lead to symptoms such as leg pain during walking (claudication), numbness, or even tissue damage in severe cases. Importantly, PAD is not confined to the extremities; it reflects a systemic atherosclerotic process that affects multiple vascular beds. As such, PAD serves as a clinical marker for widespread vascular dysfunction and is strongly associated with an elevated risk of major cardiovascular events, including myocardial infarction and stroke.

Additional secondary end points will assess participants’ adherence to medical referrals, satisfaction with the program, the number of BP screenings completed, the number of new or rediagnosed hypertensive cases, and changes in antihypertensive prescription patterns using health insurance data. Outcome assessments will be based solely on administrative records and structured questionnaires, minimizing subjectivity and measurement variability.

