### Statistical Analysis

Statistical analyses will be conducted using Stata (version 19; StataCorp). Continuous variables will be described using means and SDs when normally distributed; for skewed distributions, medians and IQR will be reported. Normality will be assessed using visual inspection of histograms and quantile-quantile plots and confirmed with the Shapiro-Wilk test.

Comparisons of continuous variables between groups (eg, before vs after the intervention and intervention vs control regions) will be performed using the Student *t* test or the Mann-Whitney *U* test, as appropriate. The Student *t* test is a statistical method used to determine whether the means of 2 independent groups are significantly different from each other. It assumes that the data in each group are approximately normally distributed and that the variances are equal or similar.

Categorical variables will be summarized as absolute frequencies and percentages. Between-group comparisons will be conducted using chi-square tests or Fisher exact tests.

All statistical comparisons will be 2-sided, and results will be considered statistically significant if *P*<.05. Corresponding 95% CIs will be reported for all estimated parameters.

The primary outcome analysis will assess the difference in stroke incidence before and after the 2-year intervention period among residents of precarious neighborhoods within the CACL of French Guiana. Stroke incidence, derived from PMSI hospitalization data, will be compared across the 2 periods using the chi-square test. To evaluate temporal trends and detect structural breaks attributable to the intervention, segmented regression of interrupted time series (ITS) [33] data will be applied. The ITS model will estimate the immediate change in level and the change in slope after the intervention, while adjusting for autocorrelation and seasonality as necessary based on model diagnostics (Figure 3).

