## Results

This study was funded in 2022 and registered on ClinicalTrials.gov in April 2023 (NCT05814068). Recruitment for this study began in September 2023 and concluded on September 4, 2025, marking the end of the 24-month intervention period. During this period, 23,289 participants benefited from the intervention (ie, received at least 1 BP measurement and health education session), including 10,901 (46.8%) who completed the full enrollment questionnaire. Three-month telephone follow-up for participants with elevated BP was conducted as scheduled and completed by December 2025. Case report form (CRF) data entry and quality monitoring procedures were in progress as of February 2026, with database lock planned for March 2026 and primary outcome analysis expected between April 2026 and May 2026.

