## Discussion

### Principal Anticipated Findings

This community-based hypertension screening intervention in French Guiana’s precarious neighborhoods is anticipated to demonstrate a significant reduction in stroke incidence among socioeconomically vulnerable populations. On the basis of the comprehensive deployment of trained health mediators who screened >23,000 participants across 32 neighborhoods, we expect to observe a 20% to 30% reduction in stroke incidence in the 2-year postintervention period compared to the 5-year baseline period. If confirmed, this would represent one of the largest quasi-experimental demonstrations of stroke prevention through community-based hypertension screening in a low- to middle-income setting in Amazonia. It is anticipated that the intervention will also result in a significant decline in other cardiovascular and renal events compared to the preintervention period.

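### The 24-month post period is the rollout itself, yet the power case and the expected 20-30% reduction assume full effect; with 46.6% of the estimated target reached, power is far below that stated.

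*Protocol article*

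**What the plan says.** **Window.** Outcome Measures sets the primary outcome as a change in stroke incidence "comparing the 5-year preintervention period with the 2-year period following the start of the intervention". The sample-size text under Statistical Analysis matches this with 60 monthly observations before and 24 after. Statistical Analysis also says the primary analysis will "assess the difference in stroke incidence before and after the 2-year intervention period", and Principal Anticipated Findings says "we expect to observe a 20% to 30% reduction in stroke incidence in the 2-year postintervention period compared to the 5-year baseline period".

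**Dates.** Results states: "Recruitment for this study began in September 2023 and concluded on September 4, 2025, marking the end of the 24-month intervention period". It gives "primary outcome analysis expected between April 2026 and May 2026".

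**Delivery.** Intervention or Treatment says "Each neighborhood will receive at least 1 intervention visit during the 24-month intervention period" and "The goal is comprehensive coverage of an estimated population of 50,000 adults in the target neighborhoods", with a planned pace of 2000 adults per month. The same section admits that the denominator is hard to fix. Results reports that "23,289 participants benefited from the intervention".

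**Effect and power.** The chi-square calculation takes precarious-population strokes from 238 to about 167 per year, a 30% fall applied to both years. The ITS statement claims more than 80% power for a slope change corresponding to a 20-30% reduction, with autocorrelation 0.3-0.5 and a coefficient of variation (CV) of 15-20%. ITS is the primary confirmatory analysis and the chi-square test a sensitivity check.

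**The concern.** The post months begin on the first day of field work. A neighborhood first visited in, say, month 20 contributes 19 months labelled as post while nobody there has been screened. Of the three descriptions of the window, one starts at intervention start and the other two read as starting once the intervention is over. A full two years after the end of field work cannot be observed by April-May 2026, only seven to eight months later.

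The effect assumption makes no allowance for this. It applies the whole 30% to both years, and the Discussion repeats 20-30% in the same sentence that cites the achieved reach. The article describes no phase-in, lag or coverage-weighted exposure.

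At stake is how a null result would be read. If the chance of detecting a real benefit is low, a non-significant result would probably be taken as failure of mediator-led screening, in a study intended to inform regional health policy.

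**Working it through.** **1. The plan's own figures.** 0.68 × 350 = 238 strokes per year, and 0.70 × 238 = 166.6, as stated. Over two years that is about 333 cases, below the 367 given as the required minimum; 367 could not be reproduced from the stated inputs. At a true 30% average reduction the count comparison is not short of power: 5 × 238 = 1190 strokes before against 333 after gives z = |ln 0.70| / √(1/1190 + 1/333) ≈ 5.75. The difficulty is whether that effect can occur in this window.

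**2. Exposed share.** Reach = 23,289 / 50,000 = 46.6%. With linear rollout (an assumption), the average share already screened over the 24 months is 0.466 × 0.5 = 23.3%.

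**3. Effect needed in screened people.** Assume also that screened adults carry a proportional share of strokes and that unscreened adults gain nothing. Then the needed effect = population reduction / average exposed share. For 50,000 adults: 0.20 / 0.233 = 86% and 0.30 / 0.233 = 129%. The smaller denominators are assumptions:

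| Adults in target | Reach | Average exposed | Needed for 20% | Needed for 30% |
|---|---|---|---|---|
| 50,000 (protocol estimate) | 46.6% | 23.3% | 86% | 129% (not attainable) |
| 40,000 (assumed) | 58.2% | 29.1% | 69% | 103% (not attainable) |
| 30,000 (assumed) | 77.6% | 38.8% | 52% | 77% |

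If the whole 46.6% had been covered from day 1, the needs would be 0.20 / 0.466 = 43% and 0.30 / 0.466 = 64%.

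**4. Power of the count comparison.** Suppose screening cuts stroke by 30% in those reached, with 50,000 adults. The window reduction is 0.30 × 0.233 = 7.0%, so about 443 strokes against 2 × 238 = 476 expected. z = |ln 0.93| / √(1/1190 + 1/443) = 1.30, power about 26%. A 50% effect gives an 11.6% reduction and about 59%.

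**5. Power of the ITS slope test.** The model has intercept, trend, level change and slope change, 60 + 24 months and known AR(1) errors, fitted by generalized least squares. The standard error of the slope change, expressed as the change at month 24, runs from 14.2% of baseline (CV 15%, autocorrelation 0.3) to 22.5% (CV 20%, autocorrelation 0.5).

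| Scenario | Change at month 24 | Slope-test power |
|---|---|---|
| 30% effect in those screened | 0.30 × 0.466 = 14% | 10-17% |
| 50% effect in those screened | 0.50 × 0.466 = 23% | 18-37% |
| Ramp reaching 20% | 20% | 14-29% |
| Ramp reaching 30% | 30% | 27-56% |
| Ramp averaging 20% | about 40% | 43-80% |
| Ramp averaging 30% | about 60% | 76-99% |

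The stated figure of more than 80% is met only if 30% is read as the average over the window, so that incidence has fallen by about 60% at month 24, and even then not at the least favourable CV and autocorrelation.

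**6. Which terms are diluted.** Under a linear ramp the chi-square comparison estimates the average, about half the final effect. The level term estimates an immediate jump that did not happen, so its power is 5%. The slope term follows the ramp from the start date and is not diluted, unless effects lag behind screening, in which case it misfits.

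**The case against.** Five points on the other side deserve weight.

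- A reader might infer that a break at the start date biases every analysis toward no effect. The documents do not support that. ITS is the primary analysis, it includes a slope change, and a slope change represents gradual uptake. Dilution applies to the chi-square comparison and the level term only.
- A reader might take 47% as a ceiling on reach and conclude that a 20-30% fall cannot plausibly appear. Neither follows. The 50,000 is an admitted estimate. Flyers, posters and local radio could affect unscreened adults, people at higher risk may have come forward more often, and visit timing is not reported. If 40% of strokes on average fell in people already screened, and screening halved their risk, a 20% reduction would result.
- The window is largely settled: the primary objective, Outcome Measures and the 60 + 24 month series are compatible, and the Discussion wording may be loose. Measuring impact during delivery is a legitimate aim. This stands, but the conflicting sentence in Statistical Analysis still needs correcting.
- Strengths and Limitations already promises coverage rates by neighborhood and subgroup exploration, and the number of screenings is a secondary end point. So coverage reporting is not absent. What is missing is any link from coverage to the effect assumption or the power statement.
- Replacing the primary model at this stage would risk a data-driven change. Dated neighborhood visit logs are not described, and 238 strokes per year over 32 neighborhoods is 238 / 12 / 32 ≈ 0.6 per neighborhood-month. This argues for an added, labelled analysis.

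**Conclusion.** The concern holds in a bounded form. The text gives incompatible descriptions of the post window, and the defined window coincides with the rollout. The 30% reduction in the sample size and the 20-30% expectation in the Discussion do not fit gradual, partial exposure.

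With 50,000 adults, linear rollout, proportional risk and no spillover, 20% on average needs about 86% among the screened and 30% is not attainable. With 30,000 adults the needs fall to 52% and 77%, still large. For a 30% effect in those screened, power is about 26% for the count comparison and 10-17% for the ITS slope test. Free of any assumption about reach, a ramp ending at a 30% reduction has 27-56% slope-test power at the plan's own CV and autocorrelation, against the stated figure of more than 80%.

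The arithmetic does not show that a benefit is impossible or that the slope estimate is biased under a linear ramp. It shows that a null result in this window would say little about whether screening works.

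**What to change.** 1. Use one window throughout: the 24 months from intervention start. Call it the rollout period, and align Outcome Measures, Statistical Analysis and Principal Anticipated Findings.
2. Restate the anticipated effect and the power for gradual, partial exposure, using the achieved reach with a range of denominators. Name the slope change as the ITS parameter to which the power statement refers, and say whether the percentage is the average over the window or the value at month 24.
3. Keep the planned ITS model and add a labelled analysis, specified before stroke counts are examined by period, with either a phase-in period or coverage-weighted exposure: cumulative adults screened over estimated adults, by month and, where dates allow, by neighborhood. If the counts have already been examined, label it post hoc. Extend the hospital discharge (PMSI) series to the latest month available.
4. State that a null result in this window does not show that screening is ineffective.

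Cost: no new field work, but some extra analysis and a later data extract. The stated power becomes less favourable, the coverage denominator stays approximate, and counts by neighborhood are sparse, so the neighborhood version may need pooling.
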